## Introduction

With increasing marijuana use, cannabinoids have become one of the most frequently encountered psychoactive substances in the blood or oral fluids of drivers who are drug-impaired or involved in motor vehicle accidents [1]. The 2015 US National Roadside Survey showed that the rate of tetrahydrocannabinol (THC)–positive drivers increased 48% among all drivers [2]. Further, THC is associated with a 50% increased risk for traffic crashes [3,4], and the risk of motor vehicle collision while driving under the influence of marijuana is twice as high as when driving unimpaired [1,5]. Opioid use is associated with a 47% increased risk of crash involvement [6,7]. Further, motor vehicle collisions are among the leading causes of unintentional morbidity and mortality in North America [8,9]. While the cause of motor vehicle collisions is multifaceted, a potential contributor is the use of psychoactive medications such as prescription opioids [6,10,11]. Due to developmental life stage, older adults have a higher risk for multiple drug use, including polypharmacy [12], which puts them at a higher risk for drug-drug interactions [13]. Driving performance involves multiple underlying components of psychomotor functioning, such as attention, executive functions, and vehicle control [14]. While the effects of acute medical marijuana and prescription opioid intoxication are known [13,15-17], how long-term use of medical marijuana affects driving performance—a complex skill needed for continued independence with age—is unknown. Additionally, there are numerous ongoing physical and cognitive changes that affect driving performance with age [18,19]. Given the proliferation of medical marijuana use and prescription opioid use in adults aged 50 years and older [20-23], the prevalence of polypharmacy, and declining functional abilities, it is imperative that we understand the long-term effects of daily medical marijuana use. Further, we need to understand how co-occurring use of medical marijuana and prescription opioids, in the presence of comorbidities such as chronic pain, affects real-world driving outcomes.

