### Study Design

We are using a two-group observational study design with a group with medical marijuana use for more than 12 months daily or most days of the week (medical marijuana group [MMG]) versus a race-sex–matched group with no marijuana exposure in the past 10 years and no history of daily use (no marijuana group [NMG]). We chose 10 years as the no–marijuana-exposure window to ensure that recreational use was not a confounder. We will test the difference between long-term medical marijuana exposure and no marijuana exposure on driving performance outcomes in adults aged 50 years and older who endorse chronic or severe nonmalignant pain through an open-road driving assessment. There will be up to 3 in-person assessment sessions over approximately 10 days. Assessment session 1 (AS1; the first assessment session) is the onboarding session, which will include informed consent, sociodemographics, a battery of psychosocial measures, and urinalysis to test for the presence of marijuana, opioids, and other commonly misused substances. After AS1, we will use ecological momentary assessment to capture medical marijuana use (MMG) or mood and medication use (NMG). MMG participants will complete twice-daily assessments of medical marijuana use for 7 days. To attention match, the NMG will complete twice-daily assessments of mood and any medication use daily for 7 days. Assessment session 2 (AS2; the second assessment session), the open-road driving performance task, will occur approximately 8 days after AS1 and, for MMG participants, 8-12 hours after the last medical marijuana use. At AS2, vision screening to ensure appropriate visual acuity and urinalysis will be completed before the drive. Additionally, we will request permission from MMG participants only to extract Office of Medical Marijuana Use (OMMU) purchase history data, which include the dispensary name, date of purchase, quantity of medical marijuana purchased, and route of administration. Assessment session 3 (AS3; the third and final assessment session) will be a qualitative interview with a subset of participants (n=60) regarding self-regulation of medical marijuana and prescription medication use, to be completed no later than 3 days after the drive (Figure 1).

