### Sample Size and Power

Power estimates for this study are based on the number needed for the subanalysis to ensure we have sufficient power to answer aim 2. Using G*Power for the *F* test, we calculated the sample size for a small effect size (*f*=0.20) based on the expectation of a smaller effect size for subgroup analyses than for the main analyses [36]. Therefore, with an α of 0.5 and power set at 80%, a total sample size of 198 is needed to detect a small effect between subgroups of medical marijuana only, medical marijuana and prescription opioids, prescription opioids only, and no use at all. However, to ensure we have the full sample needed, we are planning for a potential early termination rate (eg, drive not completed due to intoxication or other reasons) of 5%, which indicates we need a sample size of 250—as 198 + 10 (5%) = 250 (125 per group). We anticipate a medium effect size for aim 1 based on the first ROAD ACE (Reactions of Older Adults Driving After Cannabis Exposure) project (1R21DA048067) that examined driving errors and medical marijuana 7-day pattern of use in a driving simulator. We found a Pearson *r*=0.459, which is equal to a medium effect size (see preliminary data above). Therefore, we will have sufficient power to test the effects in aims 1 and 2.

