**Exclusion criteria**
Active psychosisLost or revoked driving privilegesScore below 24 (out of 30) on the Montreal Cognitive Assessment (MoCA)Control participant who tests positive for marijuana use by urine test or reports any marijuana use in the past 10 years

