### Study Procedures

#### Screening

Participants referred to the study by MMTC, community-dwelling adults who self-nominate for participation, or those identified by our recruitment specialist will undergo preliminary screening for eligibility, including questions related to chronic or severe pain, frequency of medical marijuana use, date of last marijuana use, Florida medical marijuana card status, and Florida driver’s license status, as well as basic sociodemographic information. Once eligibility has been verified, participants will be scheduled for their first assessment session. They will be instructed to bring a valid Florida driver’s license, a valid Florida medical marijuana card (MMG only), and a list of all current prescription medications, over-the-counter medications, vitamins, and supplements with the names, doses, and frequency of administration for each. Screening IDs will be separate from participant IDs, which will be assigned after study enrollment and informed consent. Screening data will be used for the Consolidated Standards of Reporting Trials (CONSORT). Figure 1 provides the study flow.

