#### Assessment Session 1 (Onboarding, Informed Consent, and Questionnaires)

At the AS1 study appointment, participants will be greeted by a study research assistant who will introduce the study and provide informed consent. Following informed consent, participants will be screened for cognitive fitness to proceed using the Mini-Mental State Examination–Second Edition Brief Version (MMSE-2:BV), a 16-item screener used to efficiently assess cognitive function [37], to ensure that participants are eligible for the study. If a participant scores fewer than 14 points on the MMSE-2:BV, the study team will administer the Montreal Cognitive Assessment (MoCA), a 30-item screener emphasizing attention and executive function that is used to detect cognitive impairment [38]. Participants must score at least 24 points on the MoCA to proceed. Participants will then complete an assessment battery that includes sociodemographic data and psychosocial measures, including detailed assessments of medical marijuana and other substance use, pain levels, and overall current health status. We will obtain the past 3-year driving record from the Division of Motor Vehicles using the current ROAD ACE protocol. Participants will be compensated US $50 for this assessment.

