#### Hypothesis 2b

Then we will check the combined effect of medical marijuana and prescription opioid on driving performance (SMS) using ANCOVA. The best fitted model we find in aim 1 will be performed in the subgroup of medical marijuana users and non–marijuana users, respectively. Thus, we will have a clear picture of the driving performance in the 4 groups: medical marijuana and prescription opioid, medical marijuana without prescription opioid, prescription opioid without medical marijuana, and no medical marijuana no prescription opioid. Thus, the combined effect can be determined.

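### The four Aim 2 cells are defined by marijuana and prescription opioids alone, and adjustment for other psychoactive drug use, which the study records, is left to a significance rule

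*Protocol article*

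**What the plan says.** The protocol article's Sample Size and Power section bases the sample size on "subgroups of medical marijuana only, medical marijuana and prescription opioids, prescription opioids only, and no use at all". Hypothesis 2b describes the same four cells as marijuana with opioid, "medical marijuana without prescription opioid, prescription opioid without medical marijuana, and no medical marijuana no prescription opioid". No third drug class enters that definition.

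The only drug-related exclusion is "Control participant who tests positive for marijuana use by urine test or reports any marijuana use in the past 10 years". The descriptions of the two study groups say that a participant may drive whatever the opioid screen shows. Nothing is said about a positive screen for another substance.

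Information on other drugs is gathered at or for the first assessment session (AS1):
- Study Design: "urinalysis to test for the presence of marijuana, opioids, and other commonly misused substances".
- Screening: participants are to bring "a list of all current prescription medications, over-the-counter medications, vitamins, and supplements", with doses and frequencies.
- Assessment Session 1: "detailed assessments of medical marijuana and other substance use, pain levels, and overall current health status".

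The Introduction itself states that "older adults have a higher risk for multiple drug use, including polypharmacy" and names psychoactive medication as a possible contributor to collisions.

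On adjustment, the Data Analysis Plan compares the marijuana and no-marijuana groups at entry on possible confounders and retains medical and demographic variables that predict outcome significantly. Hypothesis 2a selects variables by significance and adjusted R². Hypothesis 2b takes the model found best in Aim 1 and fits it separately in marijuana users and non-users.

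**The concern.** Aim 2 attributes differences in the sum of maneuvers score (SMS) to opioids, to marijuana or to both. A sedating drug taken more often by opioid users than by non-users would also lower their scores. Unless the model accounts for that drug, its effect is credited to the opioid. The same holds for marijuana in Aim 1 if co-use differs between the two main groups.

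The study has the data to deal with this but does not commit to using them. Whether co-use enters a model depends on a significance test, and for Hypothesis 2b on a model chosen for a different exposure. The baseline comparison is also made between marijuana groups, so an imbalance by opioid status would not show there. Aim 2 is the most exposed because one of its cells is small.

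**Working it through.** **1. The yardstick.** For two equal groups, f = 0.20 corresponds to a standardized difference of 2 × 0.20 = 0.40 SD. At two-sided α = 0.05 and 80% power, n per group = 2 × (1.960 + 0.842)² / 0.40² = 98.1, rounded up to 99. The total is 198, the plan's figure. (The noncentral F calculation gives 199. The α printed as 0.5 would give 54 for this test; that is a separate matter.) The plan's detectable difference for a single contrast is thus about 0.4 SD.

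**2. Cell sizes.** The article expects about 40% opioid-positive among marijuana patients and 25% among controls, with 125 per group:
- both drugs: 125 × 0.40 = 50
- marijuana without opioid: 125 − 50 = 75
- opioid without marijuana: 125 × 0.25 ≈ 31
- neither: 125 − 31 ≈ 94

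**3. Bias in an unadjusted contrast.** With no interaction, bias = (difference in co-use prevalence) × (effect of co-use on SMS in SD). The documents give neither input, so both are assumed: 10 to 30 percentage points, and 0.2 to 0.7 SD.
- Low end: 0.10 × 0.2 = 0.02 SD, which is 5% of 0.4 SD.
- High end: 0.30 × 0.7 = 0.21 SD, which is about 53% of 0.4 SD.
- Equal prevalence: 0 × effect = 0. The contrast is then noisier but not biased.

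**4. Chance that the significance rule keeps the variable.** For a yes/no covariate with prevalence p and N = 250, the standard error of its effect is about 1/√(250 × p × (1 − p)) SD, ignoring correlation with other terms. The chance of two-sided significance at 0.05 is about Φ(effect/SE − 1.96).

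| Assumed prevalence | SE (SD) | Effect 0.3 SD | Effect 0.7 SD |
|---|---|---|---|
| 20% | 0.158 | 48% | 99% |
| 10% | 0.211 | 30% | 91% |
| 5% | 0.290 | 18% | 67% |

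A moderate confounder is dropped more often than not. A strong, common one would usually be kept, provided that it is offered to the selection as one pooled variable. If each drug class is tested separately, each is rarer and more easily dropped.

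**5. Route into Hypothesis 2b.** Even if Hypothesis 2a selects co-use, Hypothesis 2b does not inherit that model. It takes the Aim 1 model, chosen with marijuana as the exposure. A co-use variable that misses the threshold in Aim 1 is absent from the combined-effect analysis.

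**6. Other sources in the protocol.** The daily surveys record medication in the no-marijuana group but marijuana use in the marijuana group, so they cannot supply a symmetric variable. The pre-drive sobriety test records nystagmus signs on the day and does not classify drug use.

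**The case against.** The strongest reply has four parts.

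*The labels are shorthand.* In a power paragraph about two exposures, a reader can take the cell names to refer to those two exposures only. This stands: Hypothesis 2b states the cells correctly, down to "no medical marijuana no prescription opioid", and no analysis relies on the power section's wording. A reader might infer that the analysis promises drug-free cells. It does not, and the label is a matter of wording.

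*A route to adjustment exists.* Medical, behavioral and clinical variables are candidates, the analyses run with and without covariates, and a full covariate list is commonly left to the analysis plan. It would be wrong to say that the protocol makes no provision, or that the urine results go unused: Expected Findings says that opioid use is measured by urinalysis on the day of the drive. But the article does not merely leave the list open. It fixes a selection rule, and the rule can discard a real confounder.

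*The study wants real-world contrasts.* The estimand compares marijuana users with people who do not consume marijuana, not with drug-free people. This also stands: admitting users of other drugs is no error in itself. It does not remove the need to separate their effect from that of the opioid.

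*The size is assumed.* This is correct. A reader might infer that users of other drugs are in fact present in every cell, or that a bias of 0.21 SD is expected. The rules only permit the first, and the second needs both extremes and no adjustment.

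**Conclusion.** The concern holds in limited form. The cells are defined by two drugs, eligibility does not restrict others, and the written selection rule does not assure adjustment for co-use that the study records. Hypothesis 2b is the weakest point because it borrows the Aim 1 model.

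The documents do not establish how large the bias would be. Under the assumed ranges it is about 0.02 to 0.21 SD for an unadjusted contrast, against about 0.4 SD detectable, and nil if co-use is equal across cells with no interaction. The upper end is the least likely to survive in the adjusted models, since a strong and common effect would usually pass the significance rule. The practical risk lies with moderate effects or less common drugs. This calls for a change that should be made; it does not invalidate the design.

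**What to change.** 1. Prespecify one yes/no variable, other psychoactive drug use, from the AS1 urine panel and the medication list. Add the drive-day (AS2) urinalysis if it uses the same panel; the article documents the wider panel for AS1 only. List the qualifying drug classes before analysis, without access to SMS.
2. Force the variable into the adjusted models for Hypotheses 1, 2a and 2b regardless of significance. The unadjusted analyses stay as planned.
3. Add a sensitivity analysis that leaves out participants positive on this variable.
4. Reword the cell labels in Sample Size and Power to match Hypothesis 2b.

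The cost is a drug classification step, one degree of freedom, and a smaller sample in the sensitivity analysis. If an assumed 10%, 20%, 30% or 40% of the 250 were left out equally from all cells, 225, 200, 175 or 150 would remain. Power for the single-contrast test at f = 0.20 and α = 0.05 would be about 0.85, 0.80, 0.75 or 0.68, and the smallest cell about 28, 25, 22 or 19. That analysis should therefore be read as supportive. With 30 participants enrolled as of November 2025, the change can be made well before analysis and needs no new data collection.

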### Participants

Participants will include 250 adults aged 50 years and older who have been registered with the state of Florida for at least 12 months to obtain medical marijuana and report use daily or most days of the week (n=125), as well as race-sex–matched participants with no marijuana use in the past 10 years and no history of daily use (n=125). Textbox 1 provides the inclusion and exclusion criteria. To examine age as an independent factor, we will ensure that age variability is balanced between the two groups. We selected a 10-year no marijuana exposure window to ensure that recreational use does not confound our findings. We chose to match participants by sex to ensure that sex differences do not account for driving performance outcomes. We also chose to match participants by race to ensure that differences in psychomotor functioning by race among older adults do not account for the findings. Groups will be balanced by age (±1 year) to allow for observation of group differences by age.

Inclusion and exclusion criteria.

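### The printed sum behind the enrolment of 250 is wrong: 198 plus a 5% allowance gives 208 to 210, and the real basis for 250 is not stated

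*Protocol article*

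**What the plan says.** The Sample Size and Power section of the protocol article gives three linked statements.

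- The requirement: "a total sample size of 198 is needed to detect a small effect between subgroups", the subgroups being the four combinations of medical marijuana and prescription opioid use.
- The allowance: "we are planning for a potential early termination rate (eg, drive not completed due to intoxication or other reasons) of 5" percent.
- The result: "198 + 10 (5%) = 250 (125 per group"). The article presents this total as what the 5% allowance leads to.

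The same enrolment is used elsewhere. The Participants section says "Participants will include 250 adults aged 50 years and older" and splits them 125 and 125. Strengths and Limitations again refers to recruiting and retaining 250.

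**The concern.** The equation is false as printed. The 10 is a correct rounding of 5% of 198, so the mistake lies in the step from the two addends to the total. It is not a misprint of 208 or 210, because 125 per group stands in the same sentence and 250 recurs in two other sections.

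This sentence is the only justification the article gives for the enrolment figure. If the 5% is right, 250 enrolled should yield about 237 completed drives. If 250 was chosen so as to end with 198, the team expects to lose about a fifth of its participants and the stated 5% is not its planning figure. These are different expectations about conduct, and they imply different power for the opioid aim. Someone monitoring retention would not know which one to hold the study to.

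**Working it through.** **Inputs**, all from Sample Size and Power: required total 198; early termination 5%; enrolment 250, as 125 per group.

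**1. The plan's own sum.**
- 5% of 198 = 0.05 × 198 = 9.9, rounded to 10. This reproduces the printed 10.
- 198 + 10 = 208, or 104 per group. The printed 250 is not reproduced; the difference is 250 − 208 = 42.

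**2. Standard inflation for loss.**
- N / (1 − loss) = 198 / 0.95 = 208.4, so 209, or 210 (105 per group) for two equal groups.
- Against 210 the gap is 250 − 210 = 40. Adding 5% and dividing by 0.95 differ by one participant before rounding to equal groups, so the choice between them does not matter here.

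**3. What 250 would require.**
- Loss that turns 250 into 198: 1 − 198/250 = 0.208, or 20.8%. Ratio to the stated rate: 20.8 / 5 = 4.2.
- As a simple add-on: 250/198 − 1 = 0.263, or 26.3%.
- Requirement that would give 250 at 5% loss: 237, since 237 / 0.95 = 249.5, rounded up to 250. The stated requirement is 198.

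**4. What 250 yields at the stated loss.**
- 250 × 0.95 = 237.5, so about 237 completers. That is 237 − 198 = 39 more than required.

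**5. What the ambiguity means for power.** The article prints "with an α of 0.5 and power set at 80" percent. The figure 198 fits alpha 0.05, not 0.5, so 0.05 is assumed here. With f = 0.20 and a noncentral F test (noncentrality f² × N), a contrast with 1 numerator degree of freedom needs 199 for 80% power, which matches 198 closely. On that basis:

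| Evaluable N | f² × N | Power, 1 df |
|---|---|---|
| 198 | 7.92 | 80% |
| 237 | 9.48 | 87% |
| 250 | 10.00 | 88% |

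Both candidate evaluable numbers meet the plan's 80% on the basis that reproduces 198.

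**6. Search for another allowance.** Cognitive screening takes place after consent (Assessment Session 1), and the exclusion criteria remove controls whose urine test is positive for marijuana. Either could cause losses beyond uncompleted drives. The article does not quantify these losses or connect them with 250.

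**The case against.** The strongest reply is that the slip is harmless. Enrolment is 250 wherever it appears, it exceeds 208, 209 and 210, and at 5% loss it leaves more than the plan says it needs. No endpoint, analysis or decision changes. That stands, and it keeps the severity down.

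A second reply is that the team may have included a further allowance, such as post-consent exclusions, and dropped it when condensing the text. That is possible, and it means a 20.8% loss is one reading among several. It does not rescue the sentence, which gives 5% as the reason for 250.

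A reader might infer four stronger things that the document does not support:

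- *That this error leaves the study underpowered.* For an overall four-group test (3 degrees of freedom, alpha 0.05, f = 0.20) power is about 64% at 198 and 73% at 237. That shortfall comes from which test 198 was computed for, a separate question, and not from the addition.
- *That the evaluable number is undefined.* The requirement is stated as 198. What is unclear is how many completers 250 is expected to give.
- *That every power statement depends on this sum.* The aim 1 statement rests on an anticipated medium effect (r = 0.459) from the earlier simulator project.
- *That about 40 people are being enrolled needlessly and enrolment should be cut.* This does not follow while the basis for 250 and the test being powered are unsettled.

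**Conclusion.** The point holds as an error in a stated derivation. From 198 and 5%, enrolment comes to 208 by the plan's own addition and 209 to 210 by the usual formula. The printed 250 is 40 to 42 higher and would correspond to 20.8% loss. The article does not account for the difference.

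The consequence is limited. The study is not short of its stated 198, since 5% loss from 250 leaves about 237. What remains is an enrolment figure that does not follow from its inputs and an expected evaluable number that could be 198 or about 237, which is 80% or 87% power on a 1-degree-of-freedom basis. The enrolment arithmetic needs no assumptions beyond the printed inputs. The power figures assume alpha 0.05 and f = 0.20. Severity is moderate.

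**What to change.** Keep 250 and correct the sentence by stating why 250 was chosen. The sponsor should supply the actual basis and not fit one to the number afterwards. One of two statements should result:

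- 250 enrolled; 5% non-completion leaves about 237 evaluable, above the 198 required; or
- 250 enrolled to allow for a total loss of about 21%, with its components named (uncompleted drives and any exclusions after consent), leaving 198 evaluable.

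In either case, restate power at the resulting evaluable number for the test actually being powered. The printed alpha of 0.5 and the degrees of freedom behind 198 should be settled as points of their own, but the restated power depends on both, so it is sensible to handle them together.

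The cost is one corrected sentence and one power calculation. Enrolment, procedures and analyses do not change. With 30 participants enrolled by November 2025 and recruitment expected to run to 2029, there is ample time to make the correction.
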